## Abstract

This paper describes the protocol for a study designed to address the high prevalence (40%) of childhood overweight and obesity in the province of Cádiz, Spain, as a reflection of what is happening worldwide. It is widely known that children who suffer from childhood obesity have a higher risk of developing chronic diseases in adulthood. This causes a decrease in the quality of life and an increase in health spending. In this context, it is necessary to intervene promoting healthy lifestyle habits from an early stage. The objective of this project will be to evaluate the effectiveness of a multimodal intervention (individual, school and family) called “PREVIENE-CÁDIZ” [CADIZ-PREVENT]. The intervention will be focused mainly on diet, physical activity, sedentary lifestyle and sleep, to prevent overweight and obesity in schoolchildren from 8 to 9 years old in the province of Cádiz. It will consist of a 10-session education program carried out in the classroom by the teachers. In addition, children will be assigned two workbooks, one to work on in class and the other at home with parents. A workshop aimed at parents will be included to help teach them how to obtain healthier lifestyle habits. The proposed study will involve a quasi-experimental design with a control group.

## 1. Introduction

The World Health Organization (WHO) considers obesity to be a problem or main issue of concern for public health today in the developed world, due to the high prevalence of this disease in these countries and all the problems it causes. Together with the International Obesity Task Force (IOTF), obesity has been classified as the epidemic of the 21st century [1,2]. The prevalence of this epidemic has increased in Spain by three to four times in the last 20 years and has not only caused a strong impact on chronic diseases, but also on health spending and the quality of life of the population [3]. Moreover, estimates have been made [4] that by 2050, obesity rates in countries of the Organization for Economic Co-operation and Development (OECD) may affect 60% of men, 50% of women and 25% of children.

In a recent study that evaluated the levels of severe obesity in child populations (6–10 years) of 21 European countries, a conclusion was made that it presented a major public health problem for a large number of countries, especially relevant in Bulgaria, Greece, Italy and Spain. This higher prevalence of obesity in southern European countries has been demonstrated in previous research [4,5], estimated at more than 40%. When the prevalence of obesity in these countries is studied specifically (Italy [6], Greece [7] or Spain), the data are confirmed. Particularly in Spain, the Aladdin study [8], which was carried out between November 2015 and March 2016, found for this age group a percentage of 39.3% with overweight or obesity. Of this percentage, 23.2% suffered overweight and 16.1% obese. The obesity was more frequent in boys than girls.

Within Spain, the province of Cádiz (Southwest) has the highest prevalence of overweight and obesity (35% children aged 6–12 years) compared to the rest of Spain, which constitutes a serious health problem in the province that has been increasing in recent years [9]. Researchers from the Andalusian School of Public Health [10] reported a similar prevalence of overweight and obesity (37%) in children aged 8–9 years in Granada (Southeast Spain). This data confirms the need to develop and reinforce public health policies that reduce these numbers.

In the general population, obesity increases the risk of numerous diseases such as diabetes, high blood pressure, dyslipidemia, cardiovascular diseases, some types of cancer, musculoskeletal disease, obstructive sleep apnea, and fatty liver disease [11,12,13,14]. Life expectancy for 40 year old people who suffer obesity is seven years less than that of one without excess weight [15]. Similarly, obesity in children and adolescents is associated with a higher prevalence of various disease risk factors, such as pre-diabetes, increased blood pressure, accumulation of cholesterol in the arteries, increased oxidative vulnerability and sleep disorders [16,17,18,19,20], increased risk of excess body weight and related diseases in adulthood [21,22]. Excess body weight is also associated with lower self-esteem and higher levels of anxiety and depression, thus reducing well-being and quality of life [20]. Similarly, a study carried out in a sample of children aged 2–9 years in eight European countries found that children who were overweight had an increased risk of poor health-related quality of life.

Due to all the problems associated with obesity that have been described in the previous paragraph, it is urgent to detect and solve this disease in the early stages of life, both to protect the general health of the population as well as to promote lifelong engagement of healthy lifestyle behaviors [23]. Children mostly depend on their family, school, health services or social institutions to acquire relevant knowledge and skills to grow into healthy adults [24]. The important influence of the environment that surrounds the child (socioeconomic, educational level, etc. of the parents) on the healthy habits of the child has been shown in numerous studies [25,26,27]. The study conducted by Spinelli et al. [25], shows that children with parents with low and medium levels of education constitute a significant risk to suffer overweight or obesity. Children whose mothers had only primary or secondary levels of education, had a higher prevalence of severe obesity than children whose mothers had high levels of education. In the province of Cádiz, the sociocultural level is low for 25% of the adult population, as reflected in a study carried out by this research group, where the educational, employment and socioeconomic level of the adult population from the province of Cádiz was analyzed [28]. Due to this, an educational intervention based on health promotion is proposed, since this type of interventions allows individuals to overcome these inequalities, reaching children of all socioeconomic levels.

A Cochrane review [29] analyzed 37 studies focused on boys and girls between the ages of 6 and 12 years old. They evaluated interventions focused on behavior change in school settings. They concluded that the impact of the interventions translated into a reduction in BMI of 0.15 kg/m^2^ in the aforementioned age group. The authors recommended that the school curriculum was reinforced, including content on healthy eating, nutritional balance, a higher level of physical activity and personal self-image. In addition, they claimed greater support from educational personnel to achieve the goals.

It has been concluded in previous studies that the school environment is the most appropriate place for the development of strategies aimed at reducing childhood overweight/obesity, especially when the family is involved [30]. Interventions in school settings have been suggested to represent a marked improvement in terms of public health, and future interventions involving children and parents jointly are recommended [31].

Also, the duration and design of the study have also been considered in various studies, suggesting a minimum duration of six months to assess changes in lifestyle habits [31], thus our intervention will last six months. In addition, performing the intervention in a school year will allow the sample to be obtained and minimize the possibility of abandonment, as previously described [32,33]. Similarly, quasi-experimental designs or clinical trials have been suggested as the most appropriate approaches for this type of study [34].

Martínez-Vizcaíno et al. [35] have shown changes in the proportion of body fat in nine-year-old schoolchildren by means of the implementation of an extracurricular program of non-competitive physical activity. Ávila-García et al. [36] analyzed interventions for the promotion of eating habits and physical education in Spanish primary school students, identifying only seven publications that met the inclusion criteria, which shows the scarcity of research in this area. In this review, it was concluded that half of the studies showed positive changes in the improvement of body composition, and all had a positive effect regarding eating habits and on an increase in physical activity. Greater family involvement was suggested as a potential factor to improve these results, as family involvement was low in all studies.

In order to shed light and evidence on possible strategies to tackle this global health problem, with special interest in young people, the project entitled “Prevention of overweight and obesity among school children in the province of Cádiz: a quasi-experimental study of the effectiveness of a multimodal intervention “PREVIENE-CÁDIZ” [CADIZ-PREVENT] is proposed. The general objective of the study will be to evaluate the effectiveness of the multimodal intervention (individual, family and school) focused on food-related lifestyle habits, physical activity, sedentarism and sleep time, to prevent overweight and obesity in school-aged children (8–9 years) in the province of Cádiz. The main hypothesis of the study is that the intervention will improve eating habits, increase levels of physical activity, reduce screen time and increase sleeping hours of parents and children, as well as reduce the prevalence of overweight and obesity of schoolchildren aged eight to nine years in the province of Cádiz in the long term.

## 2. Materials and Methods

### 2.1. Study Design and Participants

The current study will have a quasi-experimental design with a control group, which will be target children enrolled in third grade of primary education from 26 schools of the province of Cádiz. The inclusion criteria that will be used will be: children belonging to the selected school, who are in the third grade of primary school, regardless of their age, who have the informed consent signed by their parents or legal guardians, who respond to the questionnaires and who undergo to the anthropometric measurements. The exclusion criteria will be that these requirements are not met.

The total number of study participants will be between 850 and 900 children. The parents of each schoolchild will be part of that same subject (father, mother and child are the same subject of study). The sample will be divided into two groups, the intervention group and the control group. The intervention group will contain around 450 schoolchildren and will be made up of 13 of the 26 school centers which will participate in the study. In this group, pre-intervention measurements will be performed, which will be explained later. A multimodal intervention will be developed, which will also be explained in detail later. Finally, post-intervention measurements will be made, which will be the same as the pre-intervention measurements. The control group will also contain around 450 schoolchildren and will be made up of the others 13 school centers which will participate in the study. It will be made up of the same number of schoolchildren. The difference with respect to the intervention group will be that the control group will not receive any educational intervention. Only the pre- and post-intervention measurements will be taken, to later compare the results with the intervention group and find out if an effect has emerged or not.

The province of Cádiz will be divided into four areas: Campo de Gibraltar (six schools), Jerez-Costa Noroeste (five schools), Sierra de Cádiz (nine schools) and Bahía de Cádiz-La Janda (six schools) (Figure 1). In each area, there will be between 200 and 300 participants and school centers belonging to both the intervention group and the control group. This division will be made to have a sample that is as representative as possible of the entire province of Cádiz.

Both the selection of schools participating in the study and the assignment of them to the experimental group or control group will be made randomly from the list of public schools of the Cádiz Education Delegation. These randomizations will be carried out taking into account the schools belonging to each of the geographical areas in which the province of Cádiz will be divided, the socioeconomic condition of the population served, which will be determined from the Material Deprivation Index (MDI) of the section of the census in which the school is located [37], and the number of classes or corresponding lines of each center belonging to that age group. Randomization will be carried out in groups by schools, not individually. 

The group of schoolchildren will constitute the first level of analysis, and the schools will be the second level. This target population (children 8–9 years) has been selected due to the need to detect and solve the problem of childhood obesity in early stages to promote healthier lifestyle habits, and thus achieve health benefits that allow correct weight management from childhood until adulthood, and because, at this age, children are very receptive to receiving information that implies changes in habits [23].

The project, which is 80% co-financed by funds from the Andalusian Operational Program FEDER (European Regional Development Fund) 2014–2020, will conduct in accordance with the Declaration of Helsinki. The protocol has been approved by the Andalusian Biomedical Research Ethics Committee, along with approval from the Delegation of Education and Science of the province of Cádiz (PI-0007-2017, 21 March 2018). In order to guarantee this right, the guarantees of confidentiality of the data will be specified in writing to each family, by means of a letter explaining the objectives of the study, requesting their collaboration and the signed consent of participation, as well as the anonymization of the data. Participation will be voluntary and the collection of information from children will be done by the research team at the school. The questionnaires will be answered in the classroom, and a more intimate space available to the school will be used to carry out the anthropometric measurements, such as a support room, the morning classroom, the library or the gym. Schoolchildren who do not have the informed consent signed by their parents or legal guardians will not participate in the study. These schoolchildren who do not participate in the study and belong to the schools of the intervention group will receive the educational component of the intervention but will not undergo to the pre and post intervention evaluations. And the schoolchildren who do not participate in the study and belong to schools of the control group will not undergo to the pre and post intervention evaluations and of course no intervention. The data obtained in this study will be confidential and will be treated in accordance with Organic Law 3/2018, of December 5, on the Protection of Personal Data, Regulation (EU) 2016/679 of the European Parliament and of the Council, of 27 of April 2016 (General Data Protection Regulation), and in accordance with the official document of the Andalusian School of Public Health on the protection of personal data.

### 2.2. Calculation of the Sample Size

To determine the effectiveness of the intervention on the prevalence of overweight and obesity, the sample size necessary to test hypotheses has been calculated, comparing two proportions. We will compare the percentage of overweight and obesity of schoolchildren before and after the intervention in both groups (intervention and control) (paired data) and inter-group (independent data). In our case, for an estimated difference of proportions of 9% (35% vs. 26%) with a confidence level of 95% and a power of 80%, the minimum sample size required is 410 subjects in each group (intervention and control), which makes a total of 820 subjects. For the calculation of the sample, after reviewing the results obtained by different studies carried out in our environment, it has been assumed an estimated prevalence of overweight and obesity of a 35%, which was found by Villagrán et al. (2013) [9] in a population of Cádiz similar to that of this study.

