The dependent variables of our study will be BMI, skinfold thickness of the triceps, waist/hip ratio (as anthropometric variables) and the prevalence of overweight and obesity. As surrogate or intermediate variables we will analyze behaviors related to eating, physical activity and sedentary lifestyle, hours of sleep, knowledge and beliefs about eating and physical activity, as well as the physical condition (IFIS) [44,45] of the children.

In the models, possible covariates related to personal, family, school and environment characteristics will be analyzed. Especially will be analyzed: sex, birth weight, breastfeeding, sociodemographic characteristics, family socioeconomic level, level of physical activity and time of sedentary activities of the parents; behavior, knowledge and beliefs about family food and physical activity, participation of the school in the intervention and level of adherence, participation of the center in other health promotion programs, availability or use of the school canteen and the existence of health assets in the environment.

To determine the efficacy of the different components of the intervention, predictive models will be obtained for each of the outcome variables by backward multiple linear regression, in which all possible components are included and are progressively eliminated from lowest to highest contribution. To analyze the specific contribution of a certain component on a dependent variable, the semi-partial correlations will be obtained; this method allows the effect of the component to be controlled to be subtracted from the predictors being treated. The R^2^ values of the components measure their theoretical contribution and allow establishing a theoretical hierarchy among the components that will be used in the regression by blocks; by changing R^2^ the different contributions of the variables will be seen.

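### The 9-point fall in prevalence used for sizing has no stated source and is hard to square with the only pooled effect the protocol cites; baseline-adjusted BMI should lead the anthropometric analysis

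*Protocol article*

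**What the plan says.** Section 2.2 of the protocol article sets the sample size "for an estimated difference of proportions of 9% (35% vs. 26%) with a confidence level of 95% and a power of 80" per cent, and concludes that "the minimum sample size required is 410 subjects in each group (intervention and control), which makes a total of 820 subjects". The control rate has a source, a study in a similar Cádiz population: "it has been assumed an estimated prevalence of overweight and obesity of a 35" per cent. No source or rationale is given for the 26% or for the 9-point gap. Section 2.1 plans slightly more children than the minimum: "The total number of study participants will be between 850 and 900 children".

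The Introduction summarises a Cochrane review of 37 studies at ages 6-12 and reports that "the impact of the interventions translated into a reduction in BMI of 0.15 kg/m^2^ in the aforementioned age group". Section 2.4.2 gives a second quantified effect: the Barcelona programme, one of the two this project builds on, is reported to prevent one in three new cases of childhood obesity. The Granada programme has no published result.

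Section 2.4.3 classifies overweight and obesity from BMI. Section 2.5 says: "The dependent variables of our study will be BMI, skinfold thickness of the triceps, waist/hip ratio (as anthropometric variables) and the prevalence of overweight" (this last outcome also counts obesity). It plans to compare changes between groups and to use regression and multilevel models. Baseline BMI is not among the covariates it names.

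**The concern.** Overweight is a cut on BMI, so a change in mean BMI and a change in prevalence can be put on one scale once a BMI spread is assumed. On that scale the sizing difference is several times the average effect the Introduction reports for programmes of this kind. Section 2.2 nevertheless calls the 9 points an estimate.

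The stakes lie in interpretation. If the programme does about as well as the reviewed programmes did on average, a non-significant prevalence result is the likely outcome. A reader who relies on the stated 80% power could then take it as evidence that the programme does not work. The trial also holds a more sensitive measure, BMI before and after in every child, which the sizing does not use and which section 2.5 does not put first.

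**Working it through.** **Inputs from the protocol.** 35% and 26%, 95% confidence, 80% power, 410 per group (2.2); about 450 per arm, 26 schools, 850-900 children (2.1); 0.15 kg/m² (Introduction).

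**Assumed, not in the documents.** BMI SD 2.5-4.5 kg/m², normal shape, the same shift in every child; pre-post correlation 0.8 for overweight status and 0.90-0.95 for BMI; school ICC 0.01-0.05.

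**1. The plan's own figure.** With p̄ = 0.305 and a two-sided test:

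n = [1.96·√(2·0.305·0.695) + 0.8416·√(0.35·0.65 + 0.26·0.74)]² / 0.09² = (1.2762 + 0.5454)² / 0.0081 = 409.6, so 410 per group.

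This reproduces exactly; power at 410 is 80.0%.

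**2. BMI shift that 9 points would need.** z(0.74) − z(0.65) = 0.643 − 0.385 = 0.258. The shift is 0.258 × SD: 0.65 kg/m² at SD 2.5 and 1.16 kg/m² at SD 4.5, about 4 to 8 times 0.15.

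**3. Prevalence after a uniform 0.15 kg/m² shift.** p₂ = 1 − Φ(0.385 + 0.15/SD). Unadjusted power is Φ{[d√n − 1.96·√(2p̄(1−p̄))] / √(p₁(1−p₁) + p₂(1−p₂))}. For baseline adjustment, n is divided by 1 − 0.8² = 0.36.

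| SD | p₂ | Drop (points) | Power, n = 410 / 450 | Adjusted, n = 410 |
|---|---|---|---|---|
| 2.5 | 32.8% | 2.2 | 9.7% / 10.3% | 20% |
| 3.0 | 33.2% | 1.8 | 8.0% / 8.4% | 15% |
| 3.5 | 33.4% | 1.6 | 6.9% / 7.2% | 12% |
| 4.5 | 33.8% | 1.2 | 5.6% / 5.8% | 9% |

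Sensitivity: at SD 1.5 the unadjusted power is still only 20-21%. A lognormal BMI (assumed mean 17.5, SD 1.5-4) moves p₂ by about 0.1 point.

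**4. Schools.** 850/26 is about 33 children per school, so the design effect is 1 + 32·ICC: 1.32 at ICC 0.01 and 2.60 at 0.05. Unadjusted prevalence power for 0.15 kg/m² becomes about 6-9% (SD 2.5-3.5, both tails counted). The difference detectable with 80% power from 35% is no longer 9 points but about 10 (ICC 0.01) to 14 (ICC 0.05).

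**5. BMI as the outcome.** SE = SD·√(1 − r²)·√(2·DE/425), where DE is the design effect; SD 3 and a difference of 0.15:

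| r | DE | SE | 0.15/SE | Power |
|---|---|---|---|---|
| 0 (no baseline) | 1 | 0.206 | 0.73 | 11% |
| 0.90 | 1 | 0.090 | 1.67 | 39% |
| 0.95 | 1 | 0.064 | 2.33 | 65% |
| 0.90 | 2.60 | 0.145 | 1.04 | 18% |
| 0.95 | 1.32 | 0.074 | 2.03 | 53% |

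Without clustering, the range over SD 2.5-4.5 and r 0.90-0.95 is 20-80%.

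**6. Does the Barcelona figure give 26%?** Preventing one new case in three produces a 9-point gap only if 9 ÷ (1/3) = 27% of children would otherwise become new cases during the study. The figure also concerns obesity, not overweight and obesity together.

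**The case against.** The strongest reply is that the protocol nowhere claims 0.15 kg/m² as its expected effect. It is an average over 37 behaviour-change studies, and the protocol argues in the Introduction and Discussion that combining diet, activity and family involvement does better. That stands. A reader might infer that sections 1 and 2.2 contradict each other, or that the trial's true power is 6-10%. The documents support neither: the low figures are conditional on an effect of the cited size.

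The conversion also needs an SD and an equal shift in every child. If the effect were concentrated near or above the cut-off, a mean change of 0.15 would not fix the change in prevalence. That stands too, and rules out saying the trial will almost certainly find nothing. But the protocol does not argue for such a concentrated effect.

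The 6-10% is for an unadjusted comparison of final prevalence, whereas section 2.5 plans to compare changes. Hence the 9-20% above.

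It is tempting to blame dichotomisation. At the 65th percentile of a normal distribution a binary outcome keeps about 60% of the information, and unadjusted BMI has about 11% power at SD 3 against 8% for prevalence. Most of the gain comes from using the baseline value.

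Finally, section 2.5 already lists BMI first, so prevalence is not the only outcome analysed. A condensed article may also leave the basis of the 26% to the full protocol. That weakens any complaint about a missing source, but not the mismatch in size between two figures the article does print.

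**Conclusion.** The point holds in a limited form. The 410 per group is arithmetically right for its inputs. What is not supported is calling the 9 points an estimate: the article ties it to no evidence, it equals about 4 to 8 times the only pooled effect cited for the age group under a uniform shift, and the Barcelona figure, which deserves weight, does not by itself yield 26%. For an effect of the cited average size the prevalence comparison would be weak under every SD considered.

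The exact percentages rest on the assumed SD, normality, uniform shift, correlations and ICC. This is a planning value to be described accurately and an analysis order worth improving. It is not an error of calculation, and it does not show that the programme cannot achieve 9 points.

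**What to change.** **Section 2.2.** Describe the 9 points as the difference assumed for sizing under an individual-level formula. Do not present it as an estimate from the cited evidence, nor as the smallest detectable difference, because school clustering makes that larger. Add that a non-significant prevalence result would not exclude an effect of the size reported in the Introduction. If a basis for 26% exists, cite it and say how the Barcelona result bears on it.

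**Section 2.5.** Make post-intervention BMI, adjusted for baseline BMI, age and sex in the multilevel model with school as a cluster, the lead anthropometric analysis. Report it as a between-group difference with a 95% CI that can be read against 0.15 kg/m². Keep prevalence beside it as the public-health outcome.

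**Cost.** Rewording of two sections; BMI is already measured before and after in every child. The stated power will look less favourable and prevalence will no longer be the sole headline for sizing. The BMI analysis eases the shortfall for an effect of 0.15 kg/m² without removing it.

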### 2.5. Statistical Analysis

A descriptive analysis of the main outcome variables will be carried out with measures of centrality, dispersion and 95% confidence intervals (CI), and percentages or prevalence for the categorical variables. Chi square tests will be used for categorical variables and *t*-test or ANOVA for continuous variables, which will be used for comparisons of percentages or means, respectively, when they have a normal distribution. The effectiveness will be studied by comparing the changes in the groups. Simple and multiple linear regressions and/or logistic regressions with the respective odds ratios (OR) and the 95% CI will be applied as an association measure. The grouping term will be modeled in the analysis to adjust the effect of the intraclass correlation and a multilevel test will be conducted. For this, several levels of grouping will be established. The first level will be constituted by the geographical areas of study, the second by the municipality, the third level of grouping will be the school center and the line or classroom, and the fourth and last will be given by the intervention (control and experimental group).

For the analysis of longitudinal data, MANOVA of maximum likelihood and least squares will be used under conditions of normality of the data (assuming that large sample sizes will be obtained). If the data are not normal, generalized linear models (GLM) will be used. As a strategy for the analysis of missing data, the analysis of missing values of the SPSS statistical package will be used. In most situations it is not possible to verify the association of the missing data with other variables that allow it to be used to impute them in a probabilistic way; the Little’s MCAR test will be used to determine if the missing data occurs completely randomly (“Missing Completely at Random Data: MCAR”) and if its imputation is necessary. If the value of p obtained is less than 0.5, it cannot be assumed that the data are completely lost by chance and a multiple imputation will be made.

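### The 80% power for 410 children per group comes from a formula for independent children and is not supported for a trial that allocates 26 whole schools

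*Protocol article*

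**What the plan says.** Section 2.2 of the protocol article gives a complete calculation. The target is set "for an estimated difference of proportions of 9% (35% vs. 26" per cent), the error rates are given as "with a confidence level of 95% and a power of 80" per cent, and the result is that "the minimum sample size required is 410 subjects in each group (intervention and control), which makes a total of 820 subjects". The data are described as within-group and between-group comparisons: "paired data) and inter-group (independent data". The section mentions no intraclass correlation, design effect, number of schools, school size or correlation between the two measurements.

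Section 2.1 describes a different structure. There are 26 schools, 13 per group, and "Randomization will be carried out in groups by schools, not individually". Schools are named as the second level of analysis. On enrolment, "The total number of study participants will be between 850 and 900 children", with about 450 per group.

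Section 2.5 says "The grouping term will be modeled in the analysis to adjust the effect of the intraclass correlation". It also says that effectiveness will be studied by comparing changes between the groups, and it lists chi-square tests for percentages.

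**The concern.** Children in one school tend to resemble each other, and here they also receive or do not receive the programme together. When schools are allocated, the variance of the between-group difference grows with the ICC and the number of children per school, and the degrees of freedom come from the schools. The article recognises this in its analysis section but sizes the trial as if children were allocated one by one.

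At stake is how the result will be read. If the trial finds no difference, the only power statement in the article invites the conclusion that a 9-point effect was ruled out with 80% power. Section 2.6 plans to bring the results to the authorities with a view to wider implementation, so that reading could matter.

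**Working it through.** **Inputs from the article.** Proportions 0.35 and 0.26; 95% confidence; 80% power (section 2.2). 13 schools per group; about 450 children per group, 850 to 900 in total (section 2.1).

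**Assumed, because the article gives no value.** ICC 0.01, 0.02 and 0.05; pre-post correlation r of 0.5 and 0.7; equal school sizes.

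**1. Reproducing 410.** With the mean proportion 0.305:

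n = [1.960·√(2·0.305·0.695) + 0.8416·√(0.35·0.65 + 0.26·0.74)]² / 0.09²
= [1.960·0.6511 + 0.8416·0.6480]² / 0.0081 = 409.6, so 410 per group.

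This is an exact match for a two-sided test of independent proportions. A continuity correction would give 432, a one-sided test 323 and the unpooled variance 407. The design effect in the stated figure is therefore 1, and the baseline measurement plays no part in it.

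**2. Power on end values with 13 schools per group.** School size m = 450/13 = 34.6. Design effect DE = 1 + (m − 1)·ICC. Effective n = 450/DE. Standard error = √(0.4199/effective n), where 0.4199 = 0.35·0.65 + 0.26·0.74. Power is from the noncentral t with 26 − 2 = 24 df and noncentrality 0.09/SE.

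| ICC | DE | Effective n per group | SE | 0.09/SE | Power (t, 24 df) | Power (normal) | Difference detectable at 80% (t, 24 df) |
|---|---|---|---|---|---|---|---|
| 0.01 | 1.34 | 337 | 0.0353 | 2.55 | 69% | 72% | 10.2 points |
| 0.02 | 1.67 | 269 | 0.0395 | 2.28 | 59% | 62% | 11.4 points |
| 0.05 | 2.68 | 168 | 0.0500 | 1.80 | 41% | 43% | 14.1 points |

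The detectable difference keeps the control proportion at 35%. Unequal school sizes would lower power further.

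**3. What the margin over 820 covers.** The margin is 850 − 820 = 30 to 900 − 820 = 80 children. By the normal approximation, 450 per group tolerates DE = 450/409.6 = 1.099, so ICC = 0.099/33.6 = 0.0029. For 425 per group, DE = 425/409.6 = 1.038, so ICC = 0.038/31.7 = 0.0012. The margin is then used up, with nothing left for loss to follow-up.

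**4. Can more children in the same schools help?** With 13 schools per group, the number needed on end values is 410·(1 − ICC)/(1 − 410·ICC/13), by the normal approximation. This gives about 484 per group at ICC 0.005, 593 at 0.01 and 1088 at 0.02. There is no solution once the ICC exceeds 13/410 = 0.032.

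**5. Credit for the baseline.** Adjusting for the same child's baseline value multiplies the variance by about 1 − r², if r is the same within and between schools. With 450 per group and 24 df:

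| ICC | End values only | r = 0.5 (factor 0.75) | r = 0.7 (factor 0.51) |
|---|---|---|---|
| 0.01 | 69% | 81% | 93% |
| 0.02 | 59% | 71% | 86% |
| 0.05 | 41% | 51% | 68% |

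This gain belongs to baseline adjustment. A plain comparison of changes has variance factor 2(1 − r) when the two variances are equal. That is 1.00 at r = 0.5, so no gain, and 0.60 at r = 0.7.

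**The case against.** The strongest reply is that the end-value figures understate the trial. The same children are measured before and after, and section 2.5 plans to compare changes. A substantial pre-post correlation is plausible over so short an interval, and step 5 shows that 80% can then survive clustering. Section 2.1 also takes area, material deprivation and number of classes into account in the randomisation, which may reduce the variation between schools. This stands, and it limits the claim about size. It does not rescue the stated figure, because section 2.2 uses none of it and gives no correlation from which to check it.

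A second reply is that the multilevel analysis deals with clustering. It protects the error rate and the intervals, so their validity is not in question here. It does not make a power figure for independent children apply.

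A third is that a journal article condenses the full protocol. That excuses a missing detail such as the reason for the margin over 820. It does not cover section 2.2, which states its inputs, comparison and result in full.

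Some stronger readings are tempting and should be resisted:

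- A reader might infer that the number of schools alone fixes the information. Step 4 shows that more children per school can restore power on end values up to an ICC of about 0.03.
- A reader might infer that the unclustered test will never be run. Section 2.5 does list chi-square tests, alongside the multilevel model.
- A reader might set the 9-point target against the review finding in the Introduction that "the impact of the interventions translated into a reduction in BMI of 0.15" kg/m² and call the target implausible. Converting a prevalence change to a mean BMI shift needs a standard deviation and a distribution that the article does not give, and it is a separate question from clustering.

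**Conclusion.** The point holds: the 80% power in section 2.2 does not follow from the design in section 2.1 or the clustered analysis in section 2.5. The arithmetic of 410 is correct; it is the formula that does not match the allocation. For any positive ICC, 410 children per group gives less than 80% power on the comparison for which it was calculated. At the planned 450 per group, 80% on end values needs an ICC below about 0.003, even by the more lenient normal approximation.

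The size is not settled. It ranges from 69% down to 41% on end values for an ICC of 0.01 to 0.05, and from 93% down to 68% over the same range with baseline adjustment at r = 0.7. All of these rest on assumed values. A reader might conclude that the trial is badly underpowered. The documents do not show that; they show that its power has not been established.

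**What to change.** Keep the 26 schools and rewrite section 2.2. State:

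- the ICC, with a source or as a range;
- 13 schools per group, and the mean and spread of school size;
- the expected loss between the two measurements;
- the assumed pre-post correlation.

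Then give the resulting power and detectable difference for the clustered, baseline-adjusted comparison, using about 24 df. If these inputs cannot be supported, remove the claim that 820 children give 80% power.

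The cost is a rewritten paragraph and possibly a less favourable figure. No schools, children or measurements need to be added, and the intervention does not change.
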